"Therapy Tool for Anxiety Disorders" by Hagena and Gebauer (2014). The treatment manual of the control group is thematically based on that of Positive Psychotherapy, but strongly shortened. The treatment manuals of PPT and KVT each comprise 12 group sessions of 90-100 minutes each and one individual session. The treatment manual of the control group comprises 12 sessions, three of which (the first, the sixth and the twelfth) take place in an online group setting, and the remaining nine are self-completed with the help of instructional videos and e-mail communication. All therapy sessions take place online. The individual groups consist of six to eight participants. The participants in each group also have access to a website created specifically for the study. This website provides work materials, audio files and instructional videos. In addition, it offers the possibility of contacting the study director via a chat function; it also serves as a virtual bulletin board to make certain exercises visible in anonymized form. The study includes three measurement time points, a pre- and post-measurement and a follow-up after three months. The treatments are carried out by psychologists in training as clinical psychologists and psychological psychotherapists in Austria and Germany. All psychologists are intensively trained in the respective manuals, participate in regular intervision sessions and receive supervision from experienced representatives of Positive Psychology and Cognitive Behavioral Therapy at regular intervals. All group sessions are recorded and discussed in the supervision. Each session is checked for adherence to the manual. As mentioned above, the study also includes a process efficacy study. In this study the intra-session processes as well as the inter-session processes of the therapy with Positive Psychotherapy and Cognitive Behavioral Therapy will be evaluated and related to the therapy outcome. Intra-session processes are understood as all those changes that occur directly in response to specific events in the therapy session, whereas inter-session processes are defined as processes of change between two sessions that are brought about by memories and representations of the session (Orlinsky & Geller, 1993). Intra-session processes will be assessed with the help of the Berner Stundenbeurteilungsbogen für Patienten (Flückiger et al., 2010), where patients will be asked after each session whether they have experienced it and whether they think it has brought progress, on the one hand in the sense of the

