### **3c. Consequences for participants**

3.19. Risk and consequence assessment (e.g., pain, inconvenience, injury to personal integrity, and measures to avoid and/or provide for unforeseen/undesirable events).

In principle, undesirable side effects can occur during psychotherapy (Linden, & Strauß, 2018). The occurrence of undesirable side effects cannot be ruled out in the treatments planned here. However, the primary goal of the treatments is to reduce anxiety and general psychopathological symptoms and to improve general well-being and quality of life. According to the knowledge of previous studies, the risk of unpleasantness and negative developments in the field of PPT and KVT can be considered low. Cognitive behavioral therapy is the treatment of choice for anxiety disorders and has shown very good effects to date. Positive Psychotherapy aims to strengthen the resources and strengths of the participants. In the run-up to the treatment, the participants are informed that they should inform their therapists at any time if undesirable effects should occur. If the negative changes should not be reduced, the study management should be contacted by the patients or treatment providers.

In addition, participants are given the telephone number of the crisis service responsible for their area. If there are repeated complaints about adverse experiences or side effects of the therapies, a corresponding procedure for the systematic recording of such events will be implemented at the end of the treatment (T2) (e.g. INEP, Ladwig et al., 2014).

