3.22. Methods to locate, record, and report adverse effects (Describe when, by whom, and how,  
z. e.g. free questioning and/or on the basis of lists)

During the weekly therapy sessions, undesired effects or side effects of the treatments can be immediately recognized by the therapists. The therapists are required to document not only the course of the session and the interventions, but also the perceived effects and feedback from the participants (especially negative and problem-related). In the case of communication of a negative development, this must be documented in particular; if the negative development is classified as problematic or dangerous, an individual discussion must be held promptly with the participant concerned. If no adequate solution can be found, the study and/or project management should be contacted in order to work out a solution (see also above). In addition, the intervention and the supervision of the therapists offer space to reflect on possible problems and problematic developments in individual participants and to obtain professional advice from trained clinical psychologists/psychotherapists. In addition, in the event of stress or undesirable developments outside or between treatment sessions, patients are able to contact the treatment providers at any time by e-mail or contact the study or project management.

3.23. If necessary: Plan for treatment and/or care after individuals have completed their participation in the project (who will be responsible and where).

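### Harm detection during treatment leans on weekly therapist contact that the control arm lacks, and the structured harm questionnaire is used only if complaints repeat, so the 10%/15% limits may rest on uneven counts

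*Protocol*

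**What the plan says.** All references are to the protocol.

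- **Detection (3.22).** "During the weekly therapy sessions, undesired effects or side effects of the treatments can be immediately recognized by the therapists". Therapists must document negative feedback. If a development is judged problematic or dangerous, "an individual discussion must be held promptly with the participant concerned". Patients may also e-mail the treatment providers or contact the study or project management at any time.
- **Patient reports (3.19).** Participants are told before treatment that "they should inform their therapists at any time if undesirable effects should occur".
- **Structured recording (3.19).** "If there are repeated complaints about adverse experiences or side effects of the therapies, a corresponding procedure for the systematic recording"; the sentence continues "of such events will be implemented at the end of the treatment (T2", with the INEP as an example.
- **Contact by arm (2.3).** The PPT and CBT manuals "each comprise 12 group sessions of 90-100 minutes each and one individual session". The control manual also runs to 12, of which the section says: "three of which (the first, the sixth and the twelfth) take place in an online group setting, and the remaining nine are self-completed". Those nine rely on videos and e-mail contact. Participants in every group have a study website with a chat function to the study director. The control arm is outside the process study, so it does not complete the STU-P and ISF questionnaires around each session.
- **Limits (3.30).** Treatment is interrupted when at least 10% of participants show negative effects. The study is interrupted at once when more than 15% report a deterioration. The section does not say which records supply these counts, which denominator applies, or when the share is taken.

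**The concern.** The main detection route in 3.22 presumes a therapist who sees the participant every week. That does not hold for one of the three arms. What remains for control participants between live sessions is passive: someone must decide to write or call. The active arms have the same passive routes and weekly observation as well.

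The condition in 3.19 makes this worse. The questionnaire is triggered by complaints, so where few complaints surface it may never be used. If it is used, it comes after the participant's treatment has ended.

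Two things are at stake. A percentage limit is only as good as its counts, so the rule could react late to harm arising under minimal support. And a lower count of negative effects in the control arm could mean fewer observers rather than less harm, in a trial that sets minimal support against guided therapy.

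**Working it through.** **1. Contacts.** From 2.3: PPT and CBT 12 + 1 = 13 live contacts each; control 3. Ratio 3/13 = 23%. If sessions are weekly, the control gaps are 6 − 1 = 5 weeks and 12 − 6 = 6 weeks.

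**2. Limits as counts.** From 3.1 and 3.5: 165 participants, 55 per arm. At least 10% of 165 means 17 or more (0.10 × 165 = 16.5). More than 15% means 25 or more (0.15 × 165 = 24.75). The limits are stated without derivation, so there is no figure of the plan's to reproduce.

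**3. Assumptions.** The protocol gives no harm rate, no reporting share and no schedule of looks. Let h_c and h_a be the harm rates in control and in each active arm, and r the share of control harm that gets recorded; active-arm harm is taken as fully recorded. Recorded events are then Binomial(55, r·h_c) + Binomial(110, h_a). In simulation the pooled share among those treated to date is checked at 8, 16, …, 48 and 55 per arm (24 overall at the first look), and the 10% limit fires when the share is at least 0.10.

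**4. Chance that the pooled 10% limit fires, repeated looks.**

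| Control / active harm | r = 1 | r = 0.5 | r = 0.25 |
|---|---|---|---|
| 15% / 2% | 29% | 8% | 3% |
| 20% / 2% | 52% | 13% | 4% |
| 30% / 2% | 89% | 29% | 8% |
| 20% / 10% | 97% | 77% | 57% |
| 15% / 15% | 99% | 94% | 88% |
| 20% / 20% | 100% | 100% | 99% |

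**5. Single look at the end, exact binomial sums.**
- 20% / 2%, r = 1: expected events 55 × 0.20 + 110 × 0.02 = 13.2, below 17; P(≥ 17 of 165) = 16%.
- 15% in all arms: P(≥ 17) = 97% / 84% / 69% for r = 1 / 0.5 / 0.25. For the 15% limit, P(≥ 25) = 51% / 18% / 7%.
- Control arm alone at 20% harm: P(≥ 6 of 55) = 98% / 48% / 6%.

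**6. Reading.** Under-recording in control always lowers the chance of firing. The loss is large when harm is concentrated there and modest for the 10% limit when harm is similar across arms. The 16% in step 5 shows that pooling by itself dilutes harm confined to one arm, even with complete recording.

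**The case against.** The strongest case on the other side has four parts.

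- **Other channels exist.** The control arm has e-mail, the website chat to the study director, and contact persons throughout the study whose details go to all participants (3.20). Thus 3 against 13 counts live contacts, not every chance of detection, and 12 of the 13 are group sessions, where private harm may go unsaid. This stands. But these channels are open to all arms and need the participant to act, so they do not make up for the missing observation.
- **The link to 3.30 is inferred.** A reader might conclude that the limits demonstrably act on these uneven counts. The protocol does not say so, because 3.30 names no source. All arms complete the same self-report scales at T1 and T2, and therapists rate PAS and HAMA again at T2, so a deterioration limit could use symptom data. This stands as a limit on the claim. T2 still follows the participant's last session, and no in-treatment harm source with equal coverage of the arms is described.
- **The size depends on the scenario.** A reader might take 52% / 13% / 4% as the expected loss. It rests on a tenfold difference in harm that nothing in the protocol suggests; control is a shortened PPT, and 3.19 rates the risk of PPT and CBT as low. With 15% harm everywhere the limit usually fires anyway.
- **No stated hypothesis compares harms between arms.** True, so unfair comparison is a secondary matter. Timely detection is the main one.

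The treatment manuals are not shown; control e-mail support might include a wellbeing check.

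**Conclusion.** The point holds as a cheap improvement worth considering. Detection during treatment is thinner in the control arm, and the structured instrument in 3.19 is conditional on the reports it should supplement. If the limits in 3.30 rest on those reports, control harm may be under-counted and the limits may react late.

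The size cannot be fixed from the documents. Going from full to quarter reporting in control, the chance that the pooled 10% limit fires falls from 52% to 4% under 20% / 2% harm, but only from 99% to 88% under 15% in all arms. Both rest on assumed rates, assumed looks and full recording in the active arms.

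The documents do not support saying that control harm goes unrecorded or that participants are unprotected. Reporting routes exist in every arm, 3.22 requires documentation and discussion of problems that are noticed, and symptom worsening by T2 is measured alike.

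**What to change.** - **3.19:** give the negative-effects questionnaire (e.g. INEP) to all participants in all three arms at T2, unconditionally.
- **3.22:** add one identical short online negative-effects item for all arms at fixed weeks (e.g. 4 and 8), besides therapist documentation. A positive answer leads to the individual discussion already provided for.
- **3.30:** keep the overall limits, state that they use these reports, and take the share among participants treated to date. Treat a crossing in one arm as a prompt to review that arm, not as an automatic stop; this also addresses the dilution from pooling.

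The cost is a few sentences, one questionnaire and one item in the existing online survey. Downsides are a small burden on participants, slightly more contact in the minimal-support arm, and higher counts from asking. On the last: at a uniform 5% rate the pooled 10% limit fires by chance in 17% / 10% / 4% of trials with the first look at 8 / 16 / 24 per arm. If asking raises the recorded rate to 7.5%, this becomes 46% / 39% / 28%. Counting an answer only once the individual discussion confirms it, and starting the looks later, both limit this, although confirmation brings therapist judgement back in.

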3.20. What measures are taken to prevent risks?

The therapists are psychologists (Master's degree) who have extensive theoretical and practical experience in the field of clinical psychology and psychotherapy. In addition, the therapists are familiarized with the respective manuals and trained in them. All therapy sessions are recorded to ensure fidelity. All therapists receive regular supervision and conduct intervention. In the run-up to the study, the nearest crisis services are recorded and the participants are given their telephone numbers and contact details. In addition, they are informed that they will have professional contact persons throughout the entire period of the study in the treatment providers and the study and project management. All participants will be given their contact details. Before the start of the intervention, it is also determined whether the participants are suicidal or suffering from severe depression. Both are exclusion criteria for participation in the study. The therapists are given extensive information on how to proceed in an emergency situation (crisis, suicidality). You will also receive appropriate checklists in their treatment manuals. The participants are provided with a set of guidelines to help them react appropriately in the event of a crisis. In the event of acute suicidal tendencies, an individual emergency plan is first drawn up with the participants and the duty of confidentiality is enforced. The participants will be informed about the cancellation of § 37 of the Psychology Act (this will be signed by the participants in the course of the declaration of consent), and the therapists will turn to the study and/or project management, with whom possible solutions will be worked out.

3.21. Anticipated benefits or potential benefits WiFor the included participants.

Based on existing research, treatment (both PPT and CBT) is expected to result in a significant reduction in anxiety and general psychological symptoms and negative states of mind (Laireiter & Furchlehner, 2018; Fava et al., 2005). At the same time, a strong increase in positive sensitivities, well-being, and life satisfaction is expected, especially in the positive-psychological treatment conditions. Another benefit of participating in the study is that the participants will receive the treatments free of charge, which is also a great benefit in view of the sometimes very long waiting times for professional help.

3.22. Methods to locate, record, and report adverse effects (Describe when, by whom, and how,  
z. e.g. free questioning and/or on the basis of lists)

During the weekly therapy sessions, undesired effects or side effects of the treatments can be immediately recognized by the therapists. The therapists are required to document not only the course of the session and the interventions, but also the perceived effects and feedback from the participants (especially negative and problem-related). In the case of communication of a negative development, this must be documented in particular; if the negative development is classified as problematic or dangerous, an individual discussion must be held promptly with the participant concerned. If no adequate solution can be found, the study and/or project management should be contacted in order to work out a solution (see also above). In addition, the intervention and the supervision of the therapists offer space to reflect on possible problems and problematic developments in individual participants and to obtain professional advice from trained clinical psychologists/psychotherapists. In addition, in the event of stress or undesirable developments outside or between treatment sessions, patients are able to contact the treatment providers at any time by e-mail or contact the study or project management.

3.23. If necessary: Plan for treatment and/or care after individuals have completed their participation in the project (who will be responsible and where).

If problems or negative effects occur after the end of the treatments - in the follow-up period or afterwards - the participants are asked to contact the study or project management (but also the treatment providers can be contacted). If necessary, the participants can take advantage of a counseling session with these persons. The aim is to clarify the problems and work out individual solutions. It should also be determined whether the problems can be traced back to the treatment previously completed. In any case, the conversation should be documented. The solutions to the problems mentioned could include support for the person concerned in seeking help from a psychotherapist in the region, visiting their family doctor or a specialist themselves, or - in the worst case - making use of a crisis intervention center or medical facility, provided there is an indication for this. However, if necessary, the study or project management could also offer a further supportive intervention.

will be. Both are trained psychotherapists or psychotherapists in training.

3.24. Amount and procedure for the remuneration of participants (amount as well as how this is paid; e.g. travel expenses, loss of income, etc.).

No remuneration of the participants is foreseen; the participants receive free psychological treatment as indirect and immaterial remuneration (see above).

3.25. Amount and procedure for compensating participants (amount of payment and what it is paid for; e.g., pain, etc.)

The participants do not receive any compensation; no aversive stimuli are applied or severity caused.

### **3d. Other ethical aspects**

3.26. Are the participants fully informed about the nature, objective and content of the project informed?

Yes

No, reason:

3.27. Are participants being deceived?

Yes

No

If yes, description and justification:

3.28. Ethical Considerations: Identify and describe any issues that may arise.

Since the practitioners are (only) in training to become clinical psychologists or psychotherapists and have not yet completed this training, they may lack a full range of experience and a broad repertoire of methods of psychological treatment to deal with all the problems that may arise. This can be compensated by the following components:

1. fully formulated and detailed manuals,
2. an intensive enrollment with self-experience,
3. an accompanying continuous supervision, if necessary in the presence of the study leader or - if desired - the project leader
4. an accompanying regular supervision by clinically experienced experts in PPT and/or CBT,
5. the ability to have practical experience from their own internships and professional activities in psychiatry or psychosomatics and the treatment of outpatients within the framework of their training, and
6. having sufficient knowledge in the field of clinical psychology, psychotherapy and positive psychology.

It could happen that practitioners feel overwhelmed in the course of the intervention; this should be recognized quickly in the context of intervention and/or supervision and an adequate individual solution found (e.g. change of one or both practitioners). In the event of a change of therapist, the patient's continued care is ensured in good time. In the event of a change, another practitioner, who has also been intensively trained in the manuals, takes over the treatment. In this case, a controlled handover takes place.

In addition, all practitioners are selected according to the following strict criteria. These are:

- completed master studies in psychology
- Currently in training to become a psychological psychotherapist or clinical psychologist
- Clinical experience in the field of psychiatry/psychosomatics with adults
- Positive psychology lectures or seminars taken in the course of study
- Sufficient time to be able to hold regular sessions (min 6hrs per week)

If, despite comprehensive screening and initial diagnosis, a suicidal crisis does occur, the patient may be referred and/or crisis intervention initiated.

The impression could also arise that psychotherapy is being offered with this study. In order to avoid this impression, the participants are informed from the beginning that this project is not a (statutory) psychotherapy or a psychological treatment, which is carried out by a psychotherapist in private practice and which is not covered by the health insurance.

The participants sign the declaration of consent and acknowledgement of this in the consent form. The participants sign the information and acknowledgement of this in the declaration of consent.

3.29. What is the relationship between potential risks of the study and expected benefits?

In our opinion, the expected benefits of participation in the study clearly outweigh the risks. Both the participants (reduction of anxiety symptoms and improvement of general well-being), the research (important findings in a young field of research), and the

society (new mechanisms of action to increase well-being are being evaluated) benefit from this project.

3.30. According to the risk plan, when is the project to be suspended? Under which circumstances is the project cancelled?

If at least 10% of the participants show negative effects, the treatment is interrupted. If more than 15% report a deterioration, the study will be interrupted immediately and the cause will be investigated. If the study is discontinued, the participants will be supervised by experienced psychotherapists in an individual session and, if necessary, they will be supported in finding further treatment/psychotherapy.

